#### Inclusion and exclusion criteria

3.6.1

Neonates will be enrolled consecutively upon meeting the full set of Montreux criteria for the diagnosis of NARDS during hospitalization. This cohort will include infants of all gestational ages, including premature infants, provided their respiratory distress meets all five Montreux criteria. These criteria include: (1) an acute onset of symptoms within one week following a known or suspected clinical insult; (2) exclusion of respiratory distress attributable to neonatal respiratory distress syndrome (NRDS), transient tachypnoea of the newborn (TTN), or congenital anomalies; (3) radiological evidence of bilateral, diffuse irregularities, including reduced translucency or opacities, that cannot be explained by conditions such as pleural effusion, atelectasis, NRDS, TTN, or congenital anomalies; (4) absence of congenital heart disease as the cause of pulmonary oedema, with echocardiographic confirmation required to verify the origin of the oedema; and (5) the presence of an oxygenation deficit, categorized by the OI as mild (4 ≤ OI < 8), moderate (8 ≤ OI < 16), or severe (OI ≥ 16). All five criteria must be fulfilled for diagnosis.

Exclusion criteria include: (1) respiratory distress due to primary surfactant deficiency (e.g., hyaline membrane disease), TTN, or congenital lung malformations; (2) congenital heart disease resulting in pulmonary oedema; (3) known genetic syndromes or chromosomal abnormalities; (4) data that did not conform to the Montreux criteria or cases with unavailable outcome data; and (5) abandonment or death occurring within 24 h of birth.

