### Verification by regulatory authorities

5.3

A three-tiered quality control process has been established to ensure the accuracy of data entry at each hospital. Each hospital is required to designate a primary data quality controller to review all data entries. Additionally, the coordination center will appoint secondary data quality controllers at each hospital, who will sample and inspect a minimum of 30% of the data entries on a weekly basis. The Data Committee represents the third level of quality control, performing monthly reviews of at least 10% of the data entries.

To further enhance diagnostic consistency and minimize misclassification bias across centers, a central adjudication committee will be established. This committee, composed of at least two expert neonatologists blinded to the originating site, will independently review a random sample of 10% of all enrolled cases, as well as all ambiguous cases flagged by site investigators. This review ensures the uniform application of the Montreux criteria, particularly regarding radiographic interpretation and the exclusion of other etiologies. Furthermore, WeChat groups have been established at each hospital to provide real-time feedback on inspection results and facilitate necessary corrections.

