### Control of confounding and subgroup analyses

6.5

Multivariable models will adjust for key covariates (gestational age in completed weeks, birth weight z-score, sex, major comorbidities). We will perform stratified analyses by gestational age (<32 weeks, 32–36 weeks, ≥37 weeks) and present both adjusted and stratified effect estimates. To address prematurity as a potential source of confounding and misclassification (NRDS vs. NARDS), the central adjudication committee will review all ambiguous preterm cases, evaluating the timing of respiratory failure onset, radiographic features, surfactant exposure/response, and clinical course. For non-randomized treatment comparisons (e.g., ventilation strategies, surfactant use), we will use propensity score methods (matching, inverse probability weighting) and, when appropriate, instrumental variable approaches to reduce treatment selection bias. Sensitivity analyses will include restriction to term infants and to preterm strata to evaluate effect modification by prematurity.

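### Ambiguous preterm cases are sorted into NRDS or NARDS using surfactant response and clinical course, with stated blinding to site only, and surfactant use is then compared within the retained cohort

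*Protocol article*

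**What the plan says.** Section 6.5 treats prematurity as a source of misclassification between NRDS and NARDS and says that "the central adjudication committee will review all ambiguous preterm cases", "evaluating the timing of respiratory failure onset, radiographic features, surfactant exposure/response, and clinical course". It puts no time limit on the response or the course.

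Section 5.3 describes the committee as "composed of at least two expert neonatologists blinded to the originating site". It "will independently review a random sample of 10% of all enrolled cases, as well as all ambiguous cases flagged by site investigators". No other masking is stated. The purpose given is that "This review ensures the uniform application of the Montreux criteria, particularly regarding radiographic interpretation and the exclusion of other etiologies".

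The committee's answer bears on who is in the cohort. Section 3.6.1 requires "exclusion of respiratory distress attributable to neonatal respiratory distress syndrome (NRDS), transient tachypnoea of the newborn (TTN), or congenital anomalies" and lists as an exclusion "data that did not conform to the Montreux criteria or cases with unavailable outcome data". The same section says infants are enrolled consecutively once they meet all the criteria.

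Section 6.5 goes on: "For non-randomized treatment comparisons (e.g., ventilation strategies, surfactant use), we will use propensity score methods", with instrumental variables where appropriate. Death or ECMO within 28 days is the primary in-hospital outcome (section 4.1).

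**The concern.** Response to surfactant is a consequence of surfactant, and the clinical course may be one too. If either helps to decide whether an infant stays in the cohort, and surfactant use is then compared among those who stay, the comparison is conditioned on something that happened after treatment. A treated infant who improves quickly may be judged NRDS and leave, while a treated infant who does not improve stays. Propensity scores and instrumental variables deal with who receives treatment. They do not deal with selection into the cohort on a result of treatment. Stratifying by gestational age does not help either, because the selection acts inside the preterm strata.

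Two results are at stake. One is the surfactant comparison in preterm infants. The Introduction names surfactant use among the possible explanations for the mortality gap. The other is preterm mortality, which feeds the comparison with the 12.6% and 17%–24% reported elsewhere.

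**Working it through.** **Where the text leads**

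1. Surfactant response and clinical course are inputs to the NRDS/NARDS decision (6.5).
2. NRDS is outside the cohort (3.6.1), and the review covers exclusion of other etiologies (5.3). Removal of an infant judged NRDS is implied, though not spelled out.
3. Surfactant is a named treatment comparison (6.5).
4. Whenever response or course is observed after the treatment being compared, steps 1 to 3 select on a consequence of that treatment.

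**Plan figures**

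The article gives no figure for the ambiguous share, the responder share or the reclassification rate. Its planning mortality is 12.6% (section 3.6.2). The sample size reproduces: 10 × 10 = 100 deaths, and 100 / 0.126 = 793.7, rounded up to 794. The point does not rest on this. Only the 12.6% is carried forward, and every other input below is an assumption.

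**Illustration A: ambiguous preterm infants only**

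Assume no true surfactant effect, 12.6% mortality in both arms, and in each arm a low-risk share (the responders, in the treated arm) with 4% mortality.

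- Low-risk share 30%, all removed: (12.6 − 0.30 × 4) / 0.70 = 16.3%.
- Low-risk share 30%, half removed: (12.6 − 0.15 × 4) / 0.85 = 14.1%.
- Low-risk share 15%, all removed: (12.6 − 0.15 × 4) / 0.85 = 14.1%.
- Low-risk share 15%, half removed: (12.6 − 0.075 × 4) / 0.925 = 13.3%.

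| Low-risk share | Removed, treated | Removed, untreated | Treated | Untreated | RR |
|---|---|---|---|---|---|
| 30% | all | none | 16.3% | 12.6% | 1.29 |
| 30% | half | none | 14.1% | 12.6% | 1.12 |
| 15% | all | none | 14.1% | 12.6% | 1.12 |
| 15% | half | none | 13.3% | 12.6% | 1.06 |
| 30% | all | half | 16.3% | 14.1% | 1.15 |
| 30% | all | all | 16.3% | 16.3% | 1.00 |
| 30% | half | all | 14.1% | 16.3% | 0.87 |

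The last row shows that the sign is not fixed. With a true RR of 0.80, treated mortality is 0.80 × 12.6 = 10.08%. Removing all treated responders at 30% gives (10.08 − 1.2) / 0.70 = 12.7% against 12.6%, so the benefit would disappear.

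**Illustration B: whole cohort of 1,000**

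Assume no true effect, 12.6% mortality, half of infants treated, half of the treated responding with 5% mortality, an ambiguous share of 10% to 30%, 25% to 100% of ambiguous responders removed, and no untreated infants removed.

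- Smallest case (10%, 25%): 6.25 infants removed with 0.31 deaths. Treated mortality is (63 − 0.31) / 493.75 = 12.70%, OR 1.01. Overall mortality is 125.69 / 993.75 = 12.65%.
- Largest case (30%, 100%): 75 removed with 3.75 deaths. Treated mortality is 59.25 / 425 = 13.94%, OR 1.12. Overall mortality is 122.25 / 925 = 13.22%.
- Among the ambiguous infants alone, these more extreme inputs give an OR of 1.10 to 1.76. The upper end is 20.2% against 12.6%, an RR of 1.60.

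If instead 25% to 50% of ambiguous survivors in both arms leave because of a benign course, overall mortality runs from 126 / 978.15 = 12.9% to 126 / 868.9 = 14.5%. For scale, the 95% half-width around 12.6% at n = 1,000 is 1.96 × √(0.126 × 0.874 / 1000) = 2.1 points.

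**The case against.** - **The text does not place response or course after diagnosis.** Infants are enrolled on meeting the criteria, so surfactant given and course observed before then could be baseline history. This stands as a limit: the bias arises only where the information follows the treatment compared. With no cut-off stated, the later course is not ruled out.
- **Packet contents and masking may sit in procedures not shown.** The Discussion refers to detailed SOPs for diagnosis. That is fair as to missing detail. The criticism here is of what the article does state, namely the two inputs and blinding to site.
- **Untreated infants are filtered too.** Clinical course applies to every ambiguous preterm case. This stands, and it is why equal removal gives an RR of 1.00.
- **The comparison is not central.** Surfactant use is given as an example, is absent from the objectives and outcomes, and the Discussion describes such analyses as hypothesis-generating. The term-infant restriction is untouched. This lowers the weight of the point but leaves the preterm strata affected.
- **Ignoring response has its own cost.** Surfactant-responsive NRDS would stay in and could bias the comparison in favour of surfactant. This stands, and it is why results are needed both ways.

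A reader might infer that adjudicators will use death or ECMO to decide membership. The article does not say so. It names clinical course and does not state masking to outcome, so the most that can be said is that nothing stated prevents it.

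**Conclusion.** The point holds for ambiguous preterm cases. As written, membership of the cohort can depend on a consequence of the treatment later compared, and the planned adjustment methods do not reach that. The likely direction is against surfactant and towards higher preterm mortality, because surfactant response can filter only treated infants. Neither direction nor size is fixed by the article. They depend on the ambiguous share, the responder share and how many untreated infants are also removed.

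With responder shares of 15% to 30% and removal at least as heavy in the treated arm, the RR under no true effect is about 1.0 to 1.3. The 1.29 is an extreme corner (every treated responder removed, no untreated infant removed) and should not be read as an estimate. The larger OR of 1.76 needs half of the treated to respond and all of them to be removed.

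A reader might also infer that cohort mortality as a whole would be seriously distorted. The figures do not support that: the whole-cohort OR is 1.01 to 1.12, and overall mortality of 12.65% to 13.2% lies within sampling error of 12.6%. Even heavier removal of survivors reaches only 14.5%, short of 17%. This is a moderate point, cheap to settle before adjudication starts. Whether surfactant response is a valid diagnostic input is for the investigators.

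**What to change.** In sections 5.3 and 6.5:

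1. State that adjudicators are masked to death, ECMO and later outcome as well as to site.
2. Have them first record and lock a classification based on information up to the time the Montreux criteria were met.
3. Record any reclassification that rests on surfactant response or later course afterwards, as a separate label, with death, ECMO and later outcome still withheld.
4. Keep labelled infants in the dataset and base the surfactant comparison on the first classification. State which surfactant exposure counts as the treatment compared, because response to a dose given before the criteria were met would still be visible at step 2.
5. Report the surfactant comparison and preterm mortality with labelled infants kept and removed, and give the number labelled in each arm.

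The cost is some redaction of packets, a two-step form and one extra sensitivity analysis. Some true NRDS cases will remain in the first-classification cohort, and the paired results show how much they matter. Masking should be in place from the first adjudicated case, since knowledge of outcome cannot be withdrawn afterwards.

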#### Sample size determination and accrual plan

3.6.2

Although this is a descriptive cohort study, a formal sample size calculation was performed for a secondary objective of particular significance: the development of a multivariable prediction model for in-hospital mortality. In accordance with the widely accepted criterion of a minimum of 10 events per predictor variable for logistic regression, and anticipating up to 10 potential predictors, a minimum of 100 mortality events is required. Utilizing a conservative estimated mortality rate of 12.6% as derived from previous studies, it is estimated that a total cohort of at least 794 patients would be required to achieve the desired statistical power. To account for potential incomplete data and to ensure adequate power for other secondary analyses, the target sample size is set at 1,000 patients.

The enrollment target is supported by historical annual NICU admissions across the nine high-volume tertiary centers and by pilot accrual data from the coordinating center. Together, these data indicate feasibility within the planned four-year recruitment window (2025–2028). The enrollment-monitoring framework that will be implemented includes quarterly accrual reviews and formal feasibility assessments at 12 and 24 months. In the event that accrual falls below pre-defined thresholds, pre-specified contingency measures are to be enacted. The following measures are to be implemented: activation of up to 1–3 pre-identified tertiary centers in Shenzhen, Guangdong Province; temporary augmentation of research-coordinator full-time equivalents at underperforming sites to improve case ascertainment and data capture; and structured extension of the recruitment period, subject to steering-committee and ethics-committee approval. These measures are intended to ensure the viability of the study while maintaining methodological rigor.

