### Statistical analysis plan

6.1

Continuous variables will be summarized as mean ± standard deviation (SD) or median with interquartile range (IQR), depending on distribution. Categorical variables will be presented as frequencies and percentages. Group comparisons will be conducted using the student's *t*-test or Mann–Whitney *U* test for continuous variables, and the *χ*² test or Fisher's exact test for categorical variables.

Univariate logistic regression will be used to examine associations between NARDS and study outcomes. Multivariable logistic regression will then be performed to identify independent predictors. Missing data will be addressed primarily using multiple imputation by chained equations (MICE), assuming data are missing at random. Variables with excessive missingness will be excluded according to predefined thresholds, and the imputation model will be structured accordingly. Sensitivity analyses will include complete-case analysis, k-nearest neighbors (k-NN) imputation, and inverse probability weighting to evaluate the robustness of findings to loss to follow-up. A two-sided *p* < 0.05 will be considered statistically significant. All analyses and visualizations will be conducted using R software (version 4.3.3).

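### Section 6.5 evaluates effect modification by prematurity only through separate term and preterm analyses, so neither the difference in effect nor its uncertainty is estimated

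*Protocol article*

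**What the plan says.** Gestational age has three roles in section 6.5 (Control of confounding and subgroup analyses).

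- **Adjustment covariate:** "Multivariable models will adjust for key covariates (gestational age in completed weeks, birth weight z-score, sex, major comorbidities").
- **Stratifier:** "We will perform stratified analyses by gestational age (<32 weeks, 32–36 weeks, ≥37 weeks) and present both adjusted and stratified effect estimates".
- **Effect modifier:** the listed sensitivity analyses cover "restriction to term infants and to preterm strata to evaluate effect modification by prematurity".

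The third sentence names both the aim and the tool. The article mentions no product term, heterogeneity test or other contrast between strata. The only decision rule is the general one in section 6.1: "A two-sided *p* < 0.05 will be considered statistically significant".

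The sample size in section 3.6.2 rests on a mortality model ("minimum of 10 events per predictor variable for logistic regression") and not on any comparison between gestational-age groups.

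**The concern.** Effect modification by prematurity means that an effect differs between gestational-age groups. To evaluate it, one needs an estimate of that difference and a measure of its precision. A fit restricted to term infants and another restricted to preterm infants provide neither. Entering gestational age as a covariate does not help, because that model assumes one common effect for the exposure of interest.

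Without a planned contrast, the reader is left to compare two or three separate results. The natural shortcut is to note which strata pass the 5% threshold. Each stratum holds only part of the deaths, so a real and constant effect can easily reach significance in one stratum and miss it in another. A treatment comparison or risk factor could then be reported as acting only in term or only in preterm infants when the data do not show that.

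**Working it through.** **Step 1. Reproduce the plan's own figure.** Section 3.6.2 uses 10 predictors, 10 events each and 12.6% mortality ("Utilizing a conservative estimated mortality rate of 12.6% as derived from previous studies"). 10 × 10 / 0.126 = 793.7, so 794, as stated. At the target of 1,000 infants, 1,000 × 0.126 = 126 deaths are expected, to be divided among the strata. The article gives no figure for effect modification.

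**Step 2. Assumptions not in the article.** Binary exposure at 50% prevalence; 12.6% mortality in every stratum; a common odds ratio (OR) in every stratum, so no effect modification; unadjusted Wald tests at two-sided 5%; term share of 30%, 50% or 70% for two strata, and equal thirds for three.

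**Step 3. Formulas.** With p0 and p1 the mortality in unexposed and exposed infants and n the stratum size:

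- SE(log OR) = √[1/(n/2·p0) + 1/(n/2·(1−p0)) + 1/(n/2·p1) + 1/(n/2·(1−p1))]
- power q = Φ(log OR/SE − 1.96) + Φ(−log OR/SE − 1.96)
- disagreement on significance, two strata: q1(1−q2) + q2(1−q1)
- disagreement, three equal strata: 1 − q³ − (1−q)³

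**Step 4. Worked case, OR 1.8.** Average mortality of 12.6% gives p0 = 0.094 and p1 = 0.158.

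- Full cohort, n = 1,000: SE 0.196, power 85%.
- Half, n = 500: SE 0.277, power 56%; two-stratum disagreement 2 × 0.563 × 0.437 = 49%.
- Third, n = 333: SE 0.340, power 41%; three-stratum disagreement 1 − 0.409³ − 0.591³ = 72–73%.

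**Step 5. Range at 1,000 infants, with no effect modification present.**

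| Common OR | Two strata (term share 30–70%) | Three equal strata |
|---|---|---|
| 1.0 | 9.5% | 14% |
| 1.5 | 43–45% | 53% |
| 1.8 | 49–55% | 73% |
| 2.0 | 42–51% | 75% |
| 2.5 | 20–32% | 58% |

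At 794 infants, the two-stratum figures for OR 1.5, 1.8, 2.0 and 2.5 are 39–40%, 50–54%, 48–55% and 31–43%.

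**Step 6. Compare with a direct test.** In 100,000 simulated cohorts (1,000 infants, equal term and preterm halves, common OR 2.0), the two restricted analyses disagreed on significance in 41.8%. The test (b1 − b2)/√(v1 + v2), where b and v are each stratum's log OR and variance, was significant in 4.8%.

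**Step 7. What the direct test can detect.** With equal halves and OR 1 in one of them, SE(b1 − b2) is √(0.270² + 0.273²) = 0.384 for a ratio of odds ratios of 1.5. Log 1.5/0.384 = 1.06, so power is about 18%. For ratios of 2 and 3 it is about 43% and 78%.

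**The case against.** **The plan does not say that strata will be compared by significance.** This stands. Section 6.5 promises estimates, and the 5% rule in section 6.1 is general. The disagreement rates are conditional on a reading that the plan permits but does not state.

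**A condensed article may leave the interaction term to the full analysis plan.** This carries some weight, and such a plan may contain one. But the article does more than stay silent: it assigns a specific tool to a specific aim, and the tool does not deliver it.

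**Separate strata can be compared formally.** Also true. A reader might infer that restricted analyses can never test effect modification. That goes too far: the strata are disjoint, and their estimates and standard errors can be contrasted as in step 6. The gap is that no such contrast is stated.

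**The stakes are modest.** A reader might also infer that this undermines the study's explanation of regional mortality differences. The article does not support that. Its introduction mentions gestational-age profiles as a possible explanation, which is a matter of case mix and is addressed by adjustment. Effect modification by prematurity is not a listed objective or outcome, and section 6.5 calls these sensitivity analyses.

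**The rates depend on the assumed effect.** They do. They peak at moderate odds ratios and fall at both ends. The article gives no infants or deaths by gestational age, so equal strata are an assumption.

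**Conclusion.** The point holds, with moderate weight. The method stated for effect modification by prematurity yields stratum estimates but not the difference between them or its uncertainty. This follows from the text and needs no assumption.

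The size of the risk does need assumptions. If strata are judged by significance, and with 126 deaths in 1,000, 50% exposure and equal mortality across strata, false disagreement arises in about 43–55% of cohorts for two strata at a common OR of 1.5–1.8. For three equal strata it is 53–75% at 1.5–2.0. With OR 1.0 it is about 10–14%, and for two strata at OR 2.5 it is 20–32%. Chance disagreement is therefore common for moderate effects, but it is not the expected result in every setting.

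**What to change.** In section 6.5, state that effect modification by prematurity is assessed in the full cohort with an exposure-by-gestational-age interaction, using either continuous weeks or the three existing strata, with the choice fixed in advance. Report the ratio of odds ratios with its 95% confidence interval and the interaction p-value. Keep the restricted and stratified estimates as description.

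Label the analysis exploratory, and add that a non-significant interaction will not be taken as evidence of no modification, given the low power in step 7.

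The cost is one added interaction per comparison (one coefficient for continuous weeks, two for three strata) and a short addition to the text. No further data or infants are needed.
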